### *Secondary outcome measures*

For binary outcome measures (e.g. LCOS), logistic regression analyses will be used including age group and physiology as fixed effects, and site as a random effect, with unadjusted and adjusted odds ratios (ORs) and 95% CIs reported (Table 3). Survival outcomes (length of PICU stay, length of hospital stay) will be visually presented using a Kaplan-Meier plot and a Cox proportional hazard model will be used to assess differences between treatment groups with

treatment group and stratification variables as fixed effects and site as a random effect (i.e. utilising a shared frailty model). The hazard ratio and 95% CI will be presented as an estimate of treatment effect. Continuous outcomes (e.g. PELOD-2, duration of renal replacement therapy) will be analysed using linear regression adjusting for age group and physiology as fixed effects, and site as a random effect, with mean difference and 95% CI reported. If the residuals demonstrate non-normality, quantile regression will instead be used in the same manner as for the primary outcome. Key assumptions of the models will be tested and reported on (for logistic regression: specification, goodness-of-fit, absence of multicollinearity and absence of influential observations; for survival analysis: proportionality assumption, goodness-of-fit; for linear regression: specification, distribution of residuals, homoscedasticity, absence of multicollinearity, linearity).

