#### **List of planned figures**

**Figure 1.** CONSORT participant flow diagram

**Figure 2.** Cumulative incidence functions for extubation (accounting for mortality) (all patients, and the pre-specified subgroups)

**Figure 3.** Composite figure of a) bar chart depicting proportion of patients with LCOS, b) mean (and 95% CI) SaO2-ScvO2 difference, c) boxplot of lactate levels, d) boxplot of VIS score, e) mean (and 95% CI) of creatinine values, over time points 0, 6, 12, 24, 48 hours after PICU admission, f) PELOD-2 score at 0, 24, 48 hours after PICU admission, separated by treatment group

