### 404 *Primary Outcome*

405 The primary outcome of VFD will be calculated as the sum of all episodes of invasive respiratory support, which require an endotracheal tube in situ,  
406 from start of CPB and censored at 28 days after CPB start. Patients who die within this time period will be assigned a value of zero for the VFD outcome.  
407 Ventilated days do not include non-invasive ventilation or high-flow nasal cannulae. Patients who receive a tracheostomy will be counted as ventilated  
408 as long as they receive positive pressure ventilation through the tracheostomy. The individual components of VFDs (duration of invasive respiratory  
409 support from start of CPB within the first 28 days, and death within the first 28 days) will also be presented.

410

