### 411 *Secondary Outcomes*

412 The main secondary outcome is defined by a composite of presence of LCOS, extracorporeal life support (ECLS), or all-cause death.

- 413 • The presence of LCOS (21) will be calculated as a binary variable by evaluating the relevant data items at the following time-points: admission  
414 to PICU, and after six hours, 12 hours, 24 hours, and 48 hours post-PICU admission, or until the patient is discharged from PICU (whichever  
415 occurs first). Criteria for LCOS include a blood lactate level (arterial where available, if not then venous) >4 mmol/L and the presence of an  
416 oxygen extraction of greater than 35% ( $\text{SaO}_2\text{-ScvO}_2$  gradient >35%), or a high inotrope requirement operationalised as Vasoactive-Inotrope  
417 Score (VIS)  $\geq 15$  (22, 23). If these criteria are met for at least one of the above listed timepoints, the presence of LCOS is confirmed. If individual  
418 data items required for the calculation of LCOS are missing, then the patient will be assumed not to have had LCOS.

- ECLS post-CPB during the first 48 hours after CPB start.
- Mortality is defined as all-cause death within the first 28 days after CPB start.

Additional secondary outcomes include PICU and hospital length of stay, which will be measured from start time of CPB. In patients discharged alive from the PICU to the ward and readmitted within 72 hours the subsequent PICU admission duration will be added to the index admission. Length of stay (both PICU and hospital) will be censored at 28 days or when the patient was last alive, whichever occurs earlier. Patients who die during their PICU or hospital admission will be assigned the time to event.

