Process of care measures will include the use of ECLS (as defined above); duration of time with open chest post-operatively within the first 28 days (as all surgeries will have an open chest during theatre, the time measure will start with admission to PICU, and will include time spent with open chest in cases of emergency secondary reopening); treatment and duration of treatment with inhalational NO from admission to PICU post-operatively within the first 28 days; and treatment and duration of treatment with renal replacement from admission to PICU post-operatively within the first 28 days (defined as the use of peritoneal dialysis or continuous renal replacement therapy [CRRT]). Duration of treatment with inhalational NO post-operatively and duration of treatment with renal replacement post-operatively will be restricted to those patients receiving these treatments.

433 Organ dysfunction will be assessed at admission to PICU, after 24 hours and after 48 hours, and will be defined by using the cardiovascular, respiratory,  
434 renal, neurological, and haematological components of the Paediatric Logistic Organ Dysfunction-2 (PELOD-2) scores (24). If score items are missing  
435 then it will be assumed that value was normal for the purpose of the score.

436

437 Postoperative Acute Kidney Injury was assessed using serum creatinine levels to classify according to Kidney Disease: Improving Global Outcomes  
438 (KDIGO) criteria (25). Because no baseline creatinine values were available, we applied the age-specific thresholds used in PELOD-2 to define the  
439 presumed baseline creatinine values. KDIGO Stage 1 was defined as an increase in creatinine to 1.5 to 1.9 times the presumed baseline; Stage 2 as an  
440 increase 2.0 to 2.9 times; and KDIGO 3 as an increase  $\geq 3.0$  baseline and/or the use of RRT.

441

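### The SAP gives two unreconciled rules for in-hospital deaths in length of stay, and no competing-risk method for either

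*Combined protocol and SAP*

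**What the plan says.** SAP Supplementary Appendix S2 (Secondary Outcomes) has two consecutive sentences on children who die:

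- The first is a censoring rule: "Length of stay (both PICU and hospital) will be censored at 28 days or when the patient was last alive, whichever occurs earlier".
- The second appears to assign a time instead: "Patients who die during their PICU or hospital admission will be assigned the time to event". Neither sentence says whether the event is death or discharge.

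The SAP section on secondary outcome measures sets the method: "Survival outcomes (length of PICU stay, length of hospital stay) will be visually presented using a Kaplan-Meier plot and a Cox proportional hazard model", with stratification variables as fixed effects and a shared frailty for site. It adds: "The hazard ratio and 95% CI will be presented as an estimate of treatment effect". The Kaplan-Meier curves appear again in the list of planned supplementary material.

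Elsewhere the SAP deals with death explicitly. For the primary outcome, "Patients who die within this time period will be assigned a value of zero for the VFD outcome". Planned Figure 2 shows extubation as cumulative incidence with mortality allowed for. Twenty-eight-day death has its own row in Table 3 and is part of the LCOS/ECLS/death composite.

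PICU and hospital stay are among the outcomes that the SAP classes as potentially important to patients. All secondary results are declared exploratory.

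On a related point, S2 says that the durations of inhaled NO and of renal replacement "will be restricted to those patients receiving these treatments".

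**The concern.** A programmer has to give each child a time and a status. For a child who dies on day 5, the first sentence gives status censored. The second can be read as giving status event. These lead to different analyses:

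- **Death as an event.** Death and discharge are pooled, so an early death is counted as a short stay. This is the reverse of the primary outcome, where death takes the worst value.
- **Death as censoring.** One minus the Kaplan-Meier estimate no longer estimates the proportion discharged. It refers to a setting in which nobody dies, so it lies above the true proportion in both arms.

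Either way, a mortality difference between arms does not enter the length-of-stay result in a direction that a reader would expect. The coding choice would also be made outside the SAP, for an outcome that will be read as a patient-level benefit.

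The recipient-only durations are a smaller matter of the same kind. Recipients form a group defined after randomisation, yet the SAP names duration of renal replacement as an example for regression with a mean difference, and Table 3 has p-value columns for it.

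**Working it through.** **Figures in the plan.** The documents give no event count, effect size or power for length of stay. Their one sample-size figure (1,320) concerns ventilator-free days. It reproduces within 2%: 526 per arm before inflation, and 1,316 to 1,346 in total depending on how the 10% and 15% allowances are combined. It is used here only for 660 per arm.

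**Inputs from the documents.** Peri-operative mortality 2-5% (protocol 2.1). Pilot mean PICU stay 187.4 h control and 133.6 h NO (protocol Table 1). Follow-up 28 days.

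**Assumptions.** Mortality halved by NO, the 2-5% rate applied to deaths during the stay, and constant hazards. The mean stay is set at 160 h, about the midpoint of the pilot means, in both arms, so the discharge hazard is λ = 24/160 = 0.15 per day and NO has no effect on discharge.

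**Step 1: death hazard.** Solve μ/(μ+λ) × [1 − exp(−28(μ+λ))] = p. For p = 5%, μ = 0.0080; for 2.5%, μ = 0.0039; for 2%, μ = 0.0031; for 1%, μ = 0.00154.

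**Step 2: death as event.** HR = (λ+μ_NO)/(λ+μ_control).
- 5% vs 2.5%: 0.1539/0.1580 = 0.97.
- 2% vs 1%: 0.15154/0.1531 = 0.99.

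**Step 3: all three codings** (large simulation under the same model; HR above 1 means faster discharge on NO):

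| Deaths, control vs NO | Death = event | Censored at death | Competing, kept at risk to day 28 |
|---|---|---|---|
| 2% vs 1% | 0.99 | 1.00 | 1.03 |
| 5% vs 2.5% | 0.97 | 1.00 | 1.06 |

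**Step 4: another stay distribution.** Log-normal stay with median 4 days, log-SD 0.8 to 1.0, same in survivors of both arms, deaths uniform over 14 days (all assumed):

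| Deaths, control vs NO | Death = event | Censored at death | Competing |
|---|---|---|---|
| 4% vs 2% | 1.00-1.01 | 1.02-1.03 | 1.06-1.08 |
| 5% vs 2% | 1.01 | 1.04 | 1.10-1.11 |

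**Step 5: scale.** With about 1,290 events, SE(log HR) ≈ 2/√1290 = 0.056. The gap between the outer codings runs from 1.03 − 0.99 = 0.04 to about 1.11 − 1.01 = 0.10. At 5% vs 2.5% it is ln(1.06/0.97)/0.056 ≈ 1.6 standard errors.

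**Step 6: the curves.** With deaths censored, one minus Kaplan-Meier at day 28 is 1 − exp(−0.15 × 28) = 98.5% in both arms. The proportion discharged alive is λ/(λ+μ) × [1 − exp(−28(λ+μ))]: 93.8% at 5% mortality and 96.2% at 2.5%. The curves overstate discharge by 4.7 and 2.3 points, and the difference between arms disappears.

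**Step 7: with a real effect on stay.** Using the pilot means as they stand and 5% vs 2.5% deaths, the three hazard ratios are 1.37, 1.41 and 1.40. A large effect on stay would not be overturned by the coding.

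**The case against.** The two sentences can be read together, one setting the status (censored) and the other the time (bypass start to death). The SAP says that its Stata code is public, and that code may settle the matter. This shows that a contradiction in the coding is possible rather than proven. It does not remove the ambiguity from the SAP, and under the harmonised reading the Kaplan-Meier problem remains.

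A reader might infer three stronger things that the documents do not support:

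- **That death is counted as discharge.** This holds under one reading only.
- **That a survival benefit is hidden.** Death scores zero in ventilator-free days, belongs to the main composite, has its own row in Table 3 and is allowed for in Figure 2. At 660 per arm the separate death comparison has about 32% power at 2% vs 1% and 67% at 5% vs 2.5%.
- **That both codings are invalid.** A Cox model that censors deaths estimates the cause-specific hazard ratio, a legitimate quantity. Preferring a subdistribution hazard ratio is a choice of estimand.

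The arm with more deaths does not necessarily look better either. That reversal appears under constant hazards (0.97 to 0.99) but not under the log-normal model, where deaths fall later than the typical discharge. The shift is modest, rests on assumed mortality contrasts, and concerns an exploratory outcome. All of this stands.

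On the recipient-only durations, the SAP already limits those measures to description, and Table 3 also gives the proportion treated among all children. That point is therefore minor.

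**Conclusion.** The point holds as a specification gap that should be closed before unblinding. S2 does not fix how an in-hospital death enters length of stay, and the planned Kaplan-Meier and Cox analysis has no provision for death as a competing event. The consequence is either pooling of death with discharge, or curves that overstate discharge beside a valid but unlabelled cause-specific hazard ratio.

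The effect is confined to the length-of-stay results. At 2-5% mortality the hazard ratio moves by roughly 0.04 to 0.10 between codings, less than two standard errors. That size depends on mortality differences of half or more between arms and on assumed distributions of stay and of time to death, none of which the documents give. The primary outcome and the mortality comparison are unaffected.

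**What to change.** 1. Define the event for PICU and hospital stay as discharge alive, with administrative censoring at day 28.
2. Rewrite both S2 sentences so that in-hospital death is a competing event. Deleting only the second would leave deaths censored when last alive, which conflicts with keeping them at risk to day 28.
3. Replace the Kaplan-Meier plots, in the methods text and in the supplementary list, with cumulative incidence curves for discharge alive, as already planned for extubation.
4. Name the estimand of each hazard ratio: cause-specific from the planned Cox model with site frailty, and a subdistribution hazard ratio alongside it, with site as a cluster or fixed effect.
5. Label the recipient-only durations of inhaled NO and renal replacement as descriptive, and drop their between-arm p-values from Table 3.

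The cost is SAP wording and standard software commands. The small downsides are one extra model per stay outcome and a different treatment of site in the subdistribution model.

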## **Outcome measures analysis**

### *Primary outcome measure*

The primary outcome measure (VFDs censored at 28 days after CPB start) will be analysed using a Mann-Whitney test with differences between medians calculated by quantile regression using the simplex algorithm, inclusive of stratification variables (age group and physiology) and site included as fixed effects in the model. The effect estimate, corresponding 95% confidence interval (CI) and p-value will be presented. The unadjusted p-value using a Mann-Whitney test will also be presented (Table 3).

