| Process of Care Measures                                       |                     |                       |                       |                                       |                     |
| Duration of time with open chest post-operatively median (IQR) |                     |                       |                       |                                       |                     |
| Treated with inhaled Nitric Oxide post-operatively n (%)       |                     |                       |                       |                                       |                     |
| Duration of inhaled Nitric Oxide median (IQR)                  |                     |                       |                       |                                       |                     |
| Treated with renal replacement post-operatively n (%)          |                     |                       |                       |                                       |                     |
| Duration of renal replacement median (IQR)                     |                     |                       |                       |                                       |                     |
| Physiological Descriptors                                      |                     |                       |                       |                                       |                     |
| Organ dysfunction post-operatively (PELOD-2)                          |                     |                       |                       |                                       |                     |
| PICU admission median (IQR)                                    |                     |                       |                       |                                       |                     |
| 24 hours median (IQR)                                          |                     |                       |                       |                                       |                     |
| 48 hours median (IQR)                                          |                     |                       |                       |                                       |                     |
| Troponin post-operatively                                             |                     |                       |                       |                                       |                     |

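### Open-chest time appears to include zeros, so its fallback difference in medians may be an uninformative 0 beside a Mann-Whitney p-value, and Table 3 has no open-chest count

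*Combined protocol and SAP*

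**What the plan says.** SAP S2 (process of care measures) lists "duration of time with open chest post-operatively within the first 28 days". Because every chest is open during surgery, "the time measure will start with admission to PICU". Time after an emergency reopening is added.

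The same paragraph ends with a restriction that names two other durations only: "Duration of treatment with inhalational NO post-operatively and duration of treatment with renal replacement post-operatively will be restricted to those patients receiving these treatments". Open-chest time is not named.

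Table 3 gives inhaled NO and renal replacement two rows each, a count treated and a duration. Open chest has one row, "Duration of time with open chest post-operatively", shown as median (IQR).

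Under the SAP heading on secondary outcome measures, continuous outcomes "will be analysed using linear regression adjusting for age group and physiology as fixed effects, and site as a random effect". Then: "If the residuals demonstrate non-normality, quantile regression will instead be used in the same manner as for the primary outcome". For the primary outcome, that manner is a Mann-Whitney test with "differences between medians calculated by quantile regression using the simplex algorithm", adjusted for age group, physiology and site as fixed effects, plus an unadjusted Mann-Whitney p-value. Table 3 has a column for the unadjusted p-value and another for the estimate of difference.

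The SAP's analysis principles say that secondary and other outcomes will be reported as point estimates with 95% confidence intervals and treated as exploratory.

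**The concern.** A duration that is zero for many children is a mixture of two things: whether the chest was open at all, and for how long. A difference in medians sees neither while the median child in each arm sits at zero.

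A spike at zero makes non-normal residuals almost certain, so the fallback would in practice be the analysis used. The point estimate, which the SAP makes the reported result, could then be fixed at 0 by the shape of the data. A Mann-Whitney p-value in the same row could still respond to a real shift, and the row would contradict itself. With no count of children with an open chest, Table 3 offers nothing in that row group to resolve the contradiction.

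**Working it through.** **Inputs from the documents.** Start of the clock, restriction sentence, fallback rule and Table 3 layout: as set out above. Arm size: 660 (protocol 11.2 and SAP sample size).

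**The plan's own figure.** The only calculated design figure is the sample size. n per arm = 2 × (1.960 + 1.282)² / 0.2² = 525.4, so 526. The 15% and 10% allowances give 526 × 1.15 × 1.10 = 666, 526 × 1.15 / 0.9 = 673, or 526 × 1.25 = 658. All are within 3% of 660. The figure does not bear on this point except by fixing the arm size.

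**Unadjusted result.** If more than half the values in an arm are 0, its median is 0. If that is so in both arms, the difference is 0 − 0 = 0, whatever the non-zero values are.

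**How sharp the boundary is.** With true share p, the z-distance of an arm of 660 from one half is (0.5 − p) / √(p(1 − p)/660):

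- p = 0.40: 0.10 / 0.0191 = 5.2
- p = 0.45: 0.05 / 0.0194 = 2.6
- p = 0.47: 0.03 / 0.0194 = 1.5, an upper tail of about 6%

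So chance rarely lifts an arm to half unless the true share is close to it.

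**Does adjustment rescue the estimate?** Median regression on treatment, age group, physiology and five site indicators was fitted to simulated trials of 1,320 children, 12 trials per setting. These inputs are assumed, not taken from the documents: the open-chest shares, their dependence on age, physiology and site, log-normal durations with a median of 60 h, and the NO effects.

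| Open chest, control / NO | Assumed NO effect | Adjusted median difference not 0 | Mann-Whitney p < 0.05 | Mean difference, all children |
|---|---|---|---|---|
| 19% / 13% | incidence −30% | 0% of trials | 92% | −3.9 h |
| 19% / 18% | duration −40% | 0% | 17% | −6.3 h |
| 19% / 11% | both −40% | 0% | 100% | −9.1 h |
| 34% / 24%, sites differ | incidence −30% | 0% | 92% | −8.0 h |
| 44% / 32%, sites differ | incidence −30% | 0% | 100% | −9.5 h |
| 43% / 27%, sites differ | both −40% | 0% | 100% | −20.5 h |
| 47% / 28%, uniform | both −40% | 8% | 100% | −24.9 h |
| 60% / 36%, uniform | both −40% | 100% (mean −30.1 h) | 100% | −29.4 h |

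The 8% is one trial in 12. Where open chests were concentrated in the young (85-95% of them), the adjusted difference stayed at 0 with control shares of 46-49%, although the unadjusted medians differed in up to 33% of trials.

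A separate unadjusted simulation used 200 trials per setting, durations with a median of 72 h, and NO halving incidence and cutting duration by 25%. The median difference was exactly 0 in 100% of trials at control shares of 10-40% and in 98.5% at 45%. Mann-Whitney was significant in 97.5-100%.

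**The case against.** A reader might infer that the plan would hide a real effect and report no difference. The documents do not support that. The fallback follows the primary outcome's method, which includes an unadjusted Mann-Whitney p-value, and Table 3 has a column for it. On the natural reading a shift in incidence would show as a small p-value beside an estimate of 0. That is a contradictory row rather than a concealed effect, and the objection stands to that extent. It also means that part of the rank-based remedy is already planned, without the strata.

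Other output softens the loss. The upper quartile moves once more than about a quarter of an arm has open-chest time. The subgroup section promises descriptive statistics by age group and physiology, so a subgroup with more than half open would show a non-zero median.

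The zero coding is an inference from the restriction sentence and the PICU start. The SAP does not state it, and the code it cites cannot be seen here. If the analysis is in fact limited to children with an open chest, it compares a subset formed after randomisation and says nothing about how many were left open, so the count row is needed either way.

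A reader might also tie this row to the protocol's pre-planned analysis of the impact of open chest (section 3.3). That item more naturally concerns the effect of open chest on other outcomes, and nothing links it to Table 3.

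**Conclusion.** The point holds as a conditional one. If children with closed chests count as 0, and fewer than half of each arm has any open-chest time at PICU admission or after reopening, the fallback estimate is 0 even if NO changes the frequency or duration of open chest. Under the assumed shares this was so in every adjusted trial with a control share of 45% or less. It fails near one half, and it does not apply once an arm is clearly above half. A pooled share below half is not enough; the condition must hold in each arm.

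The true share is not in the documents, so whether the condition is met is unknown. It would also go too far to call the confidence interval meaningless, since its behaviour was not computed.

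The consequence is small. The SAP reports process-of-care measures for description only, and neither the primary outcome nor the trial's main conclusion depends on this row. It is a worthwhile refinement of reporting.

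**What to change.** 1. Add a Table 3 row for n (%) with an open chest at PICU admission or on later reopening, analysed by the logistic model already planned for binary outcomes. This matches the rows for inhaled NO and renal replacement.
2. State in S2 that closed chests count as 0.
3. For the duration over all children, replace the median-difference fallback with a rank-based comparison that includes the strata, for example a stratified Mann-Whitney test or a proportional-odds model.

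Protocol 7.2 already collects whether closure was delayed and when the chest was closed, so no new data items are needed for delayed closure, and the SAP's duration already counts reopening. The cost is one extra row and one changed method line. The rank result has no hours-scale estimate. It is also weak when few chests are open and only duration changes: with 19% of controls open and duration cut by 40%, Mann-Whitney was significant in 17% of simulated trials.

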## **Outcome measures**

The definition and detail of calculation of outcome measures can be found in the Supplementary Appendix (Section S2), alongside the Stata scripts written to calculate these outcomes (available on GitHub (16)). Briefly, the outcomes are:

- Primary outcome measure: VFDs within 28 days from start of CPB
- Secondary outcome measures:

- Individual VFD components (i.e. duration of mechanical ventilation, death within 28 days after CPB start)
- Individual and components of composite measure of LCOS, and/or ECLS within 48 hours after CPB start and/or death within 28 days after CPB start;
- Length of PICU stay after CPB start;
- Length of hospital stay after CPB start;
- Process of care measures:
  - Treatment with ECLS within 48 hours after CPB start;
  - Duration of postoperative time spent with open chest including unplanned chest reopening after CPB start;
  - Treatment and duration of treatment using inhalational nitric oxide postoperatively after CPB start;
  - Treatment and duration of treatment of postoperative renal replacement therapy (includes peritoneal and continuous venous-venous haemodialysis) after CPB start;
- Physiological descriptors:
  - Postoperative troponin levels during the first 24 hours postoperatively;
  - Severity and duration of postoperative organ dysfunction; and
  - Postoperative acute kidney injury (AKI) and serum creatinine levels measured during the first 24 hours.

For the purposes of analysis and reporting, LCOS within 48 hours after CPB start, ECLS within 48 hours after CPB start, death within 28 days after CPB start and length of stay in PICU and hospital are classified as potentially patient-important secondary outcomes. The remaining secondary outcomes will be reported to describe patient physiology and processes of care only.

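### Durations of renal replacement and postoperative inhaled NO are compared between arms among recipients only, which is not a randomised comparison although Table 3 is labelled intention-to-treat

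*Combined protocol and SAP*

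**What the plan says.** SAP Appendix S2 (process of care measures) defines both durations on recipients: "Duration of treatment with inhalational NO post-operatively and duration of treatment with" "renal replacement post-operatively will be restricted to those patients receiving these treatments". S2 states no such restriction for open-chest duration, and it gives no rule for a child who dies while on either support.

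The SAP section on secondary outcome measures then uses one of these durations as its example of a regression outcome: "Continuous outcomes (e.g. PELOD-2, duration of renal replacement therapy) will be analysed using linear regression". The model adjusts for age group and physiology, with site as a random effect, and yields a mean difference with 95% CI. If residuals are non-normal, quantile regression is used as for the primary outcome. The subgroup section applies the same methods, with interaction terms, to secondary outcomes.

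Table 3 is titled as an intention-to-treat analysis. It has rows for "Duration of inhaled Nitric Oxide" and "Duration of renal replacement" under columns for unadjusted p-value, difference with 95% CI, and adjusted p-value. Directly above each duration is the number and percentage treated, for example "Treated with renal replacement post-operatively".

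On status, the SAP section on outcome measures separates these rows from the outcomes it regards as important to patients: "The remaining secondary outcomes will be reported to describe patient physiology and processes of care only". The statistical principles add that secondary and other results are exploratory and not corrected for multiplicity.

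**The concern.** Whether a child needs renal replacement or inhaled NO after surgery is decided after randomisation. Protocol section 2.2 hypothesises that NO lowers secondary organ failure, so the trial itself expects the treatment to change who needs renal support. Protocol section 6.1 leaves inhaled NO to the treating clinicians. Children who receive either support in the NO arm are therefore not exchangeable with those who receive it in the control arm, and a difference in their durations mixes any effect on duration with an effect on who enters the comparison.

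The SAP section on datasets analysed says that every analysis other than the CONSORT diagram uses the intention-to-treat population. A recipients-only contrast, printed with an interval and perhaps a p-value in a table with that label, would be read as a randomised comparison. At stake is the reading of two rows and their subgroup versions: a reduction in use could be read as prolonged support.

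**Working it through.** **Inputs.** The documents give no incidence, duration or SD for either support, so there is no planned figure on this point to reproduce. The only figure taken from the plan is 660 children per arm. That figure checks for the primary outcome: 2 × (1.960 + 1.282)² / 0.2² ≈ 526 per arm, and 526 × 1.25 (10% plus 15%) ≈ 658, against 660 stated. Everything else below is assumed.

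**1. A hand example.** Assume 100 control children on renal replacement, 50 for 24 h and 50 for 96 h. NO prevents the course in 25 of the 24-h children and changes nothing else.
- Recipients, control: (50 × 24 + 50 × 96) / 100 = 60 h
- Recipients, NO: (25 × 24 + 50 × 96) / 75 = 72 h
- All randomised, control: 6,000 / 660 = 9.1 h per child
- All randomised, NO: 5,400 / 660 = 8.2 h per child (10% less)

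Nobody is harmed and total use falls, yet the recipient-only mean rises by 12 h.

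**2. A continuous version.** Assume that recipients' durations are lognormal with median 3 days and log-SD 0.9, capped at 28 days. If the shortest fraction f of courses is prevented, the new recipient median is the old (1 + f)/2 quantile, 3 × exp(0.9 × z). For f = 0.4, z at 0.70 is 0.524, giving 3 × exp(0.472) = 4.81 days.

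| f prevented | Recipient median, control | Recipient median, NO | Change in total use |
|---|---|---|---|
| 0.1 | 3.00 d | 3.36 d | −1% |
| 0.2 | 3.00 d | 3.77 d | −4% |
| 0.3 | 3.00 d | 4.24 d | −8% |
| 0.4 | 3.00 d | 4.81 d | −13% |

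**3. Simulated trials.** Same durations, 660 per arm, control incidence 5 to 30%, prevented courses drawn from the shorter half, 1,500 trials per setting, Mann-Whitney test.
- f = 0.2: recipient-only median about 0.8 days longer with NO, nominally significant in 14% (5% incidence) to 53% (30% incidence) of trials.
- f = 0.4: 1.8 to 1.9 days longer, nominally significant in 52% to more than 99%.
- All randomised children, untreated scored 0 days: mean difference −0.01 to −0.20 days over the same settings.
- At 20% incidence and f = 0.4 (132 against 79 recipients), the recipient-only test is significant for longer duration in 99% of trials. The all-patient test is significant with lower mean use under NO in about 80%. In a further 13% it is significant while the mean happens to point the other way, because the rank test responds mainly to how many children are treated.

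**4. When the artefact shrinks or disappears.**
- Prevention unrelated to severity (f = 0.4, 20% incidence): recipient-only difference 0.00 days.
- f = 0.3 from the shorter half, remaining courses 20% shorter: +0.41 days.
- The same with remaining courses 34% shorter: −0.20 days.
- Shortest 30% removed: break-even at 3.00 / 4.24 = 0.71, that is, about 29% shortening.

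**5. Deaths.** S2 scores death within 28 days as zero for VFD but has no rule for these two durations. A child who dies on support therefore contributes a truncated course, which looks favourable. The documents give nothing from which to size this.

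**The case against.** The strongest reply is about weight. These are process-of-care measures, which the SAP says it reports for description only and treats as exploratory. No primary result, sample size or stopping decision rests on them. In the hand example the reader would see 100 against 75 children treated in the row above the longer duration, and death has its own row. All of that stands, and it limits the consequence. It does not make the estimate in the duration row a randomised one; and if description is the aim, a between-arm estimate is not needed.

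A second reply is that the p-values rest on shared column headings in an empty table shell, while the SAP promises point estimates with intervals for exploratory outcomes. This stands in part. Quantile regression in the manner of the primary outcome could bring a p-value in, and for renal replacement a between-arm difference is planned in any case.

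A third is that the wrong sign depends on the scenario. This stands fully. A reader might infer that the duration rows will show NO as harmful. The documents do not support that: it needs selective prevention of short courses and too little shortening of the rest to offset it, and the plan states neither. Nor do they support a claim that excess deaths would make harm appear as benefit; the mechanism exists but its size cannot be calculated from the documents.

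**Conclusion.** The point holds as a flaw in two exploratory rows. The comparison as planned is neither randomised nor intention-to-treat, and that is so whatever the true effect of NO. Its direction is not fixed: under the assumed durations and incidences it ranges from no artefact, through about 0.8 days, to nearly 1.9 days longer in the NO arm, and it reverses once NO shortens the remaining courses enough. Only the loss of the randomised comparison is general; every size is illustrative.

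A reader might also infer that the trial's main conclusion is at risk. It is not: VFD is analysed in all randomised children with death scored as zero. The change is worth making because the present layout invites a causal reading and the correction is simple.

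**What to change.** 1. In S2 and Table 3, keep recipient-only duration of inhaled NO and of renal replacement as a descriptive median (IQR) by arm. Leave the difference and both p-value cells blank, and label the rows as recipients only.
2. In the section on secondary outcome measures, remove renal replacement duration as the regression example, and exclude both durations from the subgroup and sensitivity models.
3. If a between-arm comparison is wanted, define days alive and free of each support to day 28 in all randomised children, with death scored as zero as for VFD. Compare the arms by a rank test stratified by age group, physiology and site, or by a proportional-odds model adjusted for them. Do not use median regression: if fewer than half the children in each arm receive the support or die (an assumption), both medians are 28 and the difference is zero.

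Steps 1 and 2 change only wording, the table shell and a few model calls. Step 3 needs a short derivation. The SAP already plans to derive the durations and 28-day deaths, but the documents do not state that start and stop times are recorded for each support, so the data fields should be checked first. The downside of step 3 is that support-free days are less intuitive than time on treatment and largely re-express incidence of use and death, which Table 3 already shows. Steps 1 and 2 alone remove the problem.
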